## Abstract

**Background:** The high incidence and mortality rates of colorectal cancer (CRC) are a severe challenge in China. In patients with stage III and high-risk stage II CRC after radical resection and postoperative adjuvant chemoradiotherapy, 40–60% experience recurrence and metastasis. Several years of clinical practice have shown that traditional Chinese medicine, including Jianpi Huatan granule (JHG), effectively prevents stage III and high-risk stage II CRC recurrence and metastasis after radical resection and postoperative standard adjuvant chemotherapy. However, high-level systematic plans and evidence-based medicine are lacking in this regard. Therefore, this randomised control trial aimes to determine the efficacy of JHG in reducing stage III and high-risk stage II CRC metastasis and recurrence after radical resection and postoperative standard adjuvant chemotherapy.

**Methods:** This is a multicentre, randomised, double-blind, placebo-controlled clinical trial. Three hundred and fifty patients with stage III or high-risk stage II CRC who completed adjuvant chemotherapy after radical resection will be recruited from eight medical centres in China and randomly assigned to test (n = 175) and control (n = 175) groups at a ratio of 1:1. The test group will receive oral JHG for 3 months, whereas the control group will receive oral placebo for 3 months. The primary outcomes will be the disease-free survival and 1-, 2-, and 3-years metastasis and recurrence rates, whereas the secondary outcomes will be quality of life and circulating tumour cells. The patients will be followed-up monthly during treatment and every 3–6 months thereafter until recurrence, metastasis, death, or the end of the study.

**Trial registration:** This trial was registered at ClinicalTrials.gov (NCT03716063).

## 1 Introduction

Colorectal cancer (CRC) is one of the most common malignant tumours worldwide. A global epidemiological study of cancer showed that CRC ranks third in incidence and second in mortality resulting from tumour malignancy (Sung et al., 2021). Moreover, its annual incidence is increasing, which seriously threatens human life and health (Siegel et al., 2019). According to the 2018 global cancer statistics (Bray et al., 2018), there were an estimated 18.1 million new cancer cases and 9.6 million cancer deaths in 2018 worldwide. The annual incidence and mortality rates of CRC have recently decreased in Western countries with improvements in early cancer prevention and treatment (Siegel et al., 2018). However, in China, the incidence of CRC has been increasing annually owing to its aging population, industrialisation, and westernised diet (Li and Gu, 2005; Winkels et al., 2021). Cancer Analysis (2015) released in 2016 (Miller et al., 2016) showed that the incidence of gastrointestinal malignant tumours in China was 1,055.4 per 100,000, with a mortality rate of 689.0 per 100,000 individuals. The incidence and mortality rates of CRC account for 25% of all CRC cases. Therefore, it is essential to develop effective preventive measures and treatments for CRC.

In patients with stage III and high-risk stage II CRC, 40–60% experience recurrence, metastasis, and progression to advanced-stage disease after radical surgery and postoperative adjuvant chemoradiotherapy (Chen et al., 2016). At present, there is no internationally recognized drug for preventing metastasis and recurrence. Therefore, preventing the recurrence and metastasis of early stage CRC is essential (Wang et al., 2021). In China, traditional Chinese medicine (TCM) is widely used to treat CRC, particularly to reduce the recurrence and metastasis rates of postoperative CRC (Li and Chi, 2011; Sun et al., 2021). Clinical trials have shown that TCM achieves good results in the treatment of CRC, especially in reducing metastasis and recurrence of postoperative CRC (Pita-Fernández et al., 2015). However, most of the previous studies conducted were cohort studies (Xu et al., 2017; Yang et al., 2008); therefore, large-sample, multicentre, randomised controlled trials are needed to provide high-level evidence of the efficacy of TCM in the treatment of CRC.

Jianpi Huatan granule (JHG) is prescribed in TCM and are widely used for the treatment of CRC in clinical practice. Our research group condensed this prescription according to several clinical studies (Xu et al., 2017; Chen et al., 2019), and we hope to explore its clinical efficacy and safety more rigorously. Therefore, this multicentre, large-sample, randomised controlled trial will evaluate the efficacy of JHG in reducing stage III and high-risk stage II CRC metastases and recurrence rates after radical resection and standard adjuvant chemotherapy.

## 2 Materials and methods

### 2.1 Trial objectives and design

To evaluate the clinical efficacy of JHG in patients with stage III and high-risk stage II CRC who completed adjuvant chemotherapy after radical resection, a large-sample, multicentre, randomised, double-blind, placebo-controlled clinical trial will be conducted. Three hundred and fifty participants with stage III or high-risk stage II CRC who completed adjuvant chemotherapy after radical resection will be recruited. In- and outpatients will be recruited from eight centres (Xiyuan Hospital of China Academy of Chinese Medical Sciences, Cancer Hospital of Chinese Academy of Medical Sciences, Tianjin People’s Hospital, Beijing Chaoyang Hospital of Capital Medical University, Henan Cancer Hospital, Nanjing Hospital of TCM, Peking University First Hospital, and First Affiliated Hospital of Guiyang College of TCM). The study flow is summarised in Figure 1.

**FIGURE 1 F1:**
[figure not shown]
Flow chart of the study procedures.

### 2.2 Randomisation and blinding

A central stochastic approach will be followed. A random sequence will be generated by professional statisticians using the SAS (PROC PLAN) statistical software (SAS Institute Inc., Cary, NC, United States). Three hundred and fifty participants will be divided into test and control groups at a ratio of 1:1, with 175 cases in each group. Random seeds and sequences will be stored confidentially in opaque envelopes, and emergency unblinded envelopes will be submitted to a third party to ensure that patients, researchers, and outcome evaluators remain unaware of patient allocations. After successful screening and signing of the informed consent form, the researcher will open a random envelope and record each participant’s name, hospital number, and admission time^1^. According to the randomized results, the test group will receive JHG, whereas the control group will receive placebo (resembling JHG in appearance, color, clarity, odor and taste).

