### 2.3 Participants recruitment

#### 2.3.1 Inclusion criteria

1) Clear pathological diagnosis of CRC that conforms to Western medicine diagnostic criteria;2) Radical resection of CRC was performed, and at least 3 months of standard adjuvant chemotherapy administered before starting the trial, including preoperative neoadjuvant therapy for rectal cancer;3) TNM stage III or high-risk stage II;4) Age 18–80 years for both sexes;5) No recurrence or metastasis by imaging or doctor’s clinical judgment; and6) Provision of written informed consent.

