### 2.6 Outcomes

#### 2.6.1 Primary outcomes

1) Disease-free survival will be defined as the time from the date of randomisation to the date of recurrence, metastasis, or death from any cause.2) Recurrence and metastasis rates at 1, 2, and 3 years.

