#### 2.10.3 Statistical analysis method

1) Descriptive statistical analysis: Qualitative indicators will be described using frequency tables, percentages, or constituent ratios, while quantitative indicators will be described using mean and standard deviation or median, lower quartile (Q1), upper quartile (Q3), minimum, and maximum.2) Two groups of comparative analyses will be conducted. For qualitative data, the chi-square test, Fisher’s exact probability method, Wilcoxon rank-sum test, Cochran–Mantel–Haenszel-2 test, and weighted least-squares covariance test will be used. Quantitative data will be tested for normal distribution using a *t*-test (homogeneity test of variance between groups with a test level of 0.05, and the Satterthwaite method for correction of the *t*-test results when the variance is uneven). The Wilcoxon rank-sum test will be used in cases of non-conformity to the normal distribution, Kaplan–Meier survival analyses will be performed, and the Cox proportional risk model will be used for survival data. The hypothesis test uses a bilateral test and generates test statistics and corresponding P values. The test level will be set at 0.05, and statistical significance will be set at P < 0.05.

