## 3 Discussion

The current treatment of stage II and III CRC involves a combination of surgery, radiotherapy, and chemotherapy (Munro et al., 2015; Snelgrove et al., 2015). Prognosis is determined according to clinical stage and risk factors (Oh et al., 2019). Patients are identified as incurable once the tumour recurs and metastasizes resulting in the death of nearly all patients (Ohlsson and Pålsson, 2003; Primrose et al., 2011). For tumours with high mortality rates, it is necessary to shift the focus from diagnosis and treatment to prevention. TCM has been widely used as a medical tool in China for cancer treatment. In previous studies, approximately 60–70% of patients with cancer in China received TCM (Sun et al., 2017; Sun et al., 2018). TCM treatment is also considered part of a healthy lifestyle to improve postoperative survival (Ching and Mok, 2022). Our research team has conducted a series of studies to prove the efficacy and safety of TCM in CRC treatment (Guo et al., 2012; Xu et al., 2017). TCM practitioners have also verified its safety and efficacy for cancer prevention and treatment in clinical practice (Liu et al., 2018; Lv et al., 2019).

To improve the clinical efficacy of TCM in the treatment of CRC and promote its use, further research into disease and syndrome combinations according to the main pathogenesis of CRC using strict multicentre clinical evaluations is necessary. In this study, patients with stage III CRC and high-risk stage II CRC after radical surgery and standard adjuvant chemotherapy will be selected as primary research participants. This large-sample, multicentre, double-blind, randomised controlled trial aims to demonstrate the efficacy of TCM in treating postoperative CRC by reducing metastasis and recurrence rates and improving patient quality of life.

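### Stage is called prognostic, but no stratification by stage is named for allocation or for the DFS test: a small loss of precision, not a bias

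*Protocol article*

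**What the plan says.** All places are in the protocol article.

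- **Population.** Section 2.3.1 admits "TNM stage III or high-risk stage II". The share of each is not given.
- **Allocation.** Section 2.2: "A random sequence will be generated by professional statisticians using the SAS (PROC PLAN) statistical software", and "Three hundred and fifty participants will be divided into test and control groups at a ratio of 1:1, with 175 cases in each group". No stratification factor is named.
- **Primary time-to-event outcome.** Section 2.6.1: "Disease-free survival will be defined as the time from the date of randomisation to the date of recurrence, metastasis, or death from any cause".
- **Sizing.** Section 2.9 uses a log-rank test with 3-year rates of 18% and 31%, 80% power and a two-sided 5% level. It expects 88 events in 342 patients and mentions no strata.
- **Analysis.** Section 2.10.3: "Kaplan–Meier survival analyses will be performed, and the Cox proportional risk model will be used for survival data". No term or stratum is listed.
- **Prognosis.** Section 3: "Prognosis is determined according to clinical stage and risk factors".

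**The concern.** The article identifies stage as a determinant of prognosis. Stage is an eligibility item, so it is known for every patient before allocation. Even so, neither the allocation nor the survival methods, as described, make use of it.

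With about 88 events, two modest costs follow if stage is in fact unused. First, the arms can differ in their stage III share by chance, which adds random error to the unadjusted hazard ratio. Second, a log-rank test that pools patients of different prognosis is somewhat less sensitive than one that compares like with like within stage. In addition, if the handling of stage is not fixed in advance, it could be chosen after the results are known.

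**Working it through.** **1. The plan's own figures (section 2.9).** With exponential survival, HR = ln(0.82)/ln(0.69) = 0.535.

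- Events for 80% power at two-sided 5%: Freedman, (1.96 + 0.842)² × [(1 + 0.535)/(1 − 0.535)]², gives 86. Schoenfeld, 4 × (1.96 + 0.842)²/(ln 0.535)², gives 81.
- With 1 year of uniform accrual, 3 further years of follow-up and 5% annual loss, 171 per arm yields 32.4 + 55.3 = 87.7 events. The plan states 33 + 55 = 88.
- Freedman's 86 events need about 335 patients. The plan states 342.

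The sizing therefore reproduces closely. Nothing below changes it.

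**2. How large a chance stage imbalance can be.** The stage mix is assumed. For a stage III share p and 175 per arm, the SD of the between-arm difference is √[2p(1 − p)/175]. At p = 0.7 this is √(2 × 0.7 × 0.3/175) = 0.049. Normal tail areas give:

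| Stage III share (assumed) | SD, points | P(gap > 5 points) | P(gap > 10 points) |
|---|---|---|---|
| 50% | 5.3 | 35% | 6% |
| 60% | 5.2 | 34% | 6% |
| 70% | 4.9 | 31% | 4% |
| 80% | 4.3 | 24% | 2% |

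**3. What such an imbalance does to the unadjusted hazard ratio.** Let h be the stage III v II hazard ratio (assumed) and d the gap. As an approximation, the ratio of mean hazards with no treatment effect is [1 + (h − 1)(p + d/2)]/[1 + (h − 1)(p − d/2)]. At p = 0.7:

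| h | d = 5 points | d = 10 points |
|---|---|---|
| 1.5 | 1.019 | 1.038 |
| 2 | 1.030 | 1.061 |
| 2.5 | 1.037 | 1.076 |

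This is the 2–8% range. The upper end depends on the assumptions. With h = 3, a 10-point gap gives 2.5/2.3 = 1.087 at p = 0.7, and 2.1/1.9 = 1.105 at p = 0.5. A gap above 10 points has only a 2–6% chance.

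**4. Error rate and power.** Simulation with 350 patients, unstratified allocation and 3,000 trials per row, using the event rates, accrual and loss of section 2.9. Each cell shows the unstratified test, then the stage-stratified test.

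| Stage III share | h | SD of centre log-hazard | Type I error | Power | Gain, points |
|---|---|---|---|---|---|
| 70% | 1.5 | 0 | 5.4% / 5.5% | 83.1% / 83.2% | 0.1 |
| 70% | 2 | 0 | 4.3% / 4.5% | 81.5% / 82.6% | 1.1 |
| 70% | 2 | 0.3 | 4.6% / 4.5% | 81.7% / 82.5% | 0.8 |
| 70% | 2.5 | 0.3 | 5.4% / 5.5% | 81.5% / 83.0% | 1.5 |
| 50% | 2.5 | 0.3 | 4.9% / 4.9% | 79.5% / 81.6% | 2.1 |

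The simulation standard error is about √(0.05 × 0.95/3,000) = 0.4 points for the error rate, so these values are consistent with 5%. Widening the assumptions to 50–80% stage III and h from 1.5 to 3 keeps the error near 5% and puts the gain at about 0 to 3 points.

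**5. Centre.** In the same simulations, stratifying the test by the eight centres, or by all 16 stage-by-centre cells, changed power by −2 to +1 points. Sixteen cells would hold about 350/16 = 22 patients and 88/16 = 5.5 events each.

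**The case against.** The strongest reply is that this is silence, not error. A journal article condenses the full protocol, and Cox terms and strata are commonly left to an analysis plan that is not shown. Section 2.2 speaks of one sequence being generated but uses the plural when it describes storage, and 175 per arm overall is compatible with stratified lists. Section 2.10.3 also lists a Cochran–Mantel–Haenszel test, though for qualitative data and with no stratifier named. Unstratified central randomisation of 350 patients is a valid design, and in most of the simulated settings the unstratified test still exceeds the planned 80% power.

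Much of this stands, and it rules out several stronger readings that a reader might infer:

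- **That one unstratified list is used and the arms are compared without stage or centre.** The article does not say so. It only names no factor and no model terms.
- **That the DFS comparison is biased or its error rate inflated.** Chance imbalance under valid randomisation is random error already covered by the 5% level, and the simulated error rates agree.
- **That omitting stage wrongly pulls the hazard ratio toward 1.** The overall and within-stage hazard ratios are different quantities. The gap between them is not a mistake in the plan.
- **That differences between sites distort the result.** No section reports such differences. They would matter only where the arms are unbalanced within a site, and centre strata bring no consistent gain.

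The reply does not remove the narrower point. Section 2.2 gives the software, ratio, arm sizes and concealment but no factor, and the DFS methods as written leave stage out although the same article calls it prognostic.

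**Conclusion.** The point holds as a minor improvement in precision, for stage only. As described, allocation and the DFS analysis make no use of a baseline factor that the article itself calls prognostic. Validity is not at issue. The cost is about 0 to 3 points of power, and a chance 5–10 point stage gap would shift the unadjusted hazard ratio by about 2–8%, small beside the design value of 0.535.

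These sizes rest on assumptions that the article does not supply: 50–80% stage III and a stage hazard ratio of 1.5–3 for the power range, and 70% with 1.5–2.5 for the 2–8% range. If the full protocol or analysis plan already stratifies by stage, only the article's description needs completing. No case is made for centre as an analysis stratum.

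**What to change.** - **Section 2.10.3.** Make the primary DFS test a log-rank test stratified by stage (III v high-risk II). Estimate the hazard ratio from a Cox model stratified by stage, and say that it is a within-stage ratio. Fix this before unblinding.
- **Section 2.2.** If randomisation has not been done, generate the PROC PLAN sequence in permuted blocks stratified by stage, and say so. If it has been done, state which factors were used or that there were none, and change the analysis text alone.
- **Centre.** It need not be an analysis stratum.

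The cost is a few lines of text and, if still possible, of the randomisation program. No new data, patients or sample-size calculation is needed, because stage is already recorded for eligibility.

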### 2.3 Participants recruitment

#### 2.3.1 Inclusion criteria

1) Clear pathological diagnosis of CRC that conforms to Western medicine diagnostic criteria;2) Radical resection of CRC was performed, and at least 3 months of standard adjuvant chemotherapy administered before starting the trial, including preoperative neoadjuvant therapy for rectal cancer;3) TNM stage III or high-risk stage II;4) Age 18–80 years for both sexes;5) No recurrence or metastasis by imaging or doctor’s clinical judgment; and6) Provision of written informed consent.

#### 2.3.2 Exclusion criteria

1) History of previous or combined malignancies except cured basal cell carcinoma of the skin and carcinoma *in situ* of the cervix;2) Presence of severe heart, liver, or kidney disease;3) Any unstable condition that may endanger patient safety and compliance with research, such as pregnancy, depression, manic–depressive disorder, obsessive–compulsive disorder, or schizophrenia; and4) Researcher determination that a patient is unsuitable for the study.

#### 2.3.3 Dropout criteria

1) All participants who signed the informed consent form and will be screened for trial eligibility will be referred to as exfoliated cases whenever and for any reason they withdrew from the study and failed to complete the observation period stipulated in the plan;2) When a participant falls behind, the researcher will contact them as much as possible to request reasons and record the last medication time to complete the evaluation project; and3) When participants withdraw owing to adverse events or ineffective treatment, the researchers will take appropriate treatment measures according to the actual participant’s situation.

#### 2.3.4 Suspension/exit criteria

1) The researchers may decide to end/suspend patient participation when the participant appears unsuitable to continue. For all cases of trial termination, the withdrawal reasons and dates will be recorded, and the reasons will be statistically analysed at the end of the study; and2) The following will be the criteria for terminating a case:a) Severe adverse events (life-threatening or impaired normal work and life) which will prevent treatment continuation;b) Severe, persistent allergic reactions that cause treatment discontinuation, in which case the treatment will be considered ineffective;c) Serious violation of the experimental plan;d) Absence or withdrawal from the trial;e) Endpoint of observation (tumour recurrence or metastasis) or inability to take Chinese herbal medicine orally; andf) Other.

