### 2.7 Follow-up

#### 2.7.1 Follow-up time

The patients will be followed-up monthly during treatment and every 3–6 months thereafter until recurrence, metastasis, death, or the end of the study.

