#### 2.10.1 Selection of analytical data sets

1) *Full analysis set:* The ideal set of participants will match the principle of intentionality analysis (mainly including all randomised participants) as closely as possible. The dataset was obtained by eliminating all randomised participants using the smallest and most reasonable method.2) *Compliance scheme set:* In compliance with the experimental treatment scheme, the main variables can be measured, baseline variables will not be missing, and no major violations of the experimental scheme will be observed.3) *Safety set:* All participants will receive at least one treatment after randomisation.4) The full analysis set and compliance scheme set will be subjected to curative effect analysis, whereas the full analysis set will be used to analyse demographic and other baseline characteristics and therapeutic indicators.

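### Section 2.3.4 merges stopping study medication with leaving the trial, in conflict with sections 2.7.1 and 2.7.3, so most of the 3-year DFS follow-up may be lost for patients who stop early

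*Protocol article*

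**What the plan says.** Section 2.3.4 opens at the level of the patient, not the drug: "The researchers may decide to end/suspend patient participation when the participant appears unsuitable to continue". It continues "For all cases of trial termination, the withdrawal reasons and dates will be recorded", and then gives a list introduced by "The following will be the criteria for terminating a case". Items a and b are severe adverse events and allergic reactions that stop treatment. Item c is "Serious violation of the experimental plan". Item d is absence or withdrawal. Item e reads "Endpoint of observation (tumour recurrence or metastasis) or inability to take Chinese herbal medicine orally". Item f is a residual category. Item b adds a consequence: "in which case the treatment will be considered ineffective". Nothing in the section says that recurrence, metastasis and death are still collected once a case is terminated.

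Section 2.7.1 sets the end of follow-up differently. After treatment, patients are seen every 3 to 6 months "thereafter until recurrence, metastasis, death, or the end of the study". Section 2.7.3 adds telephone contact up to the observation deadline or an endpoint event, and makes the last day of contact the deadline. Section 2.3.3 asks researchers to try to contact participants who fall behind.

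Section 2.6.1 defines DFS from randomisation to recurrence, metastasis or death from any cause. Section 2.4 fixes treatment at 3 months, and Table 2 schedules recurrence assessment and imaging to month 36.

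Section 2.10.1 aims the full analysis set at intention-to-treat, mainly all randomised participants, and then says: "The dataset was obtained by eliminating all randomised participants using the smallest and most reasonable method".

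**The concern.** A patient who stops the granules in month 2 because of an adverse reaction falls under both rules. Section 2.3.4 makes this a terminated case with a withdrawal date. Section 2.7.1 keeps the patient under observation, because stopping medication is not among its reasons for ending follow-up. Sites cannot apply both, and eight centres may resolve the conflict differently.

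If 2.3.4 prevails, the primary endpoint is not collected for that patient over nearly all of the 3 years. An SAP can define censoring and analysis sets, but it cannot recover recurrences that no one recorded. The certain cost is lost events. The possible further cost is bias, if patients who leave have a different prognosis and leave in different proportions by arm. Unequal exit is conceivable, because section 2.4 gives the placebo only 10% of the JHG dosage, but the document does not report it.

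**Working it through.** **1. The two rules for a patient who stops early**

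| Event | Section 2.3.4 | Sections 2.7.1 and 2.7.3 |
|---|---|---|
| Recurrence or metastasis | case terminated | follow-up ends |
| Adverse event or allergy stopping treatment | case terminated | not a reason to end follow-up |
| Serious plan violation | case terminated | not a reason to end follow-up |
| Cannot take the medicine by mouth | case terminated | not a reason to end follow-up |

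The rules agree on the first row and conflict on the other three.

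**2. The plan's own sample size**

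Inputs from section 2.9: 3-year rates of 18% and 31%, 1:1 allocation, 80% power, two-sided 5%, loss of 5% a year, 1 year of recruitment plus 3 years of follow-up.

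- HR = ln(0.82)/ln(0.69) = 0.535.
- Freedman events = (1.96 + 0.842)² × [(1 + 0.535)/(1 − 0.535)]², which gives 86 after rounding up.
- Yearly hazards: h = −ln(0.82)/3 = 0.0662 (test) and −ln(0.69)/3 = 0.1237 (control). Loss hazard: −ln(0.95) = 0.0513.
- Event probability with uniform accrual over 1 year and k = h + 0.0513: (h/k) × {1 − [exp(−3k) − exp(−4k)]/k} = 0.190 (test) and 0.323 (control).
- Required N = 336, against 342 stated. Expected events at 171 per arm = 32.4 + 55.3 = 87.7, against 33 + 55 = 88 stated.

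The design reproduces and is not in dispute.

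**3. Power if early leavers are not followed**

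Assumption: a share f of each arm is terminated during treatment and censored at about 1.5 months (0.125 year), on top of the 5% annual loss.

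Events at 175 per arm = 175(1 − f)(0.1896 + 0.3232) + 175f × [(1 − exp(−0.125 × 0.0662)) + (1 − exp(−0.125 × 0.1237))].

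Power = Φ(√events × (1 − HR)/(1 + HR) − 1.96).

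| f in each arm | Events | Power |
|---|---|---|
| 0 | 89.8 | 0.82 |
| 5% | 85.5 | 0.80 |
| 10% | 81.2 | 0.78 |
| 15% | 76.9 | 0.76 |
| 20% | 72.6 | 0.73 |

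**4. Bias with no true effect**

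Assumptions: true 3-year risk of 31% in both arms; leavers have m times the hazard of those who stay and contribute no follow-up. For each arm, solve (1 − f)(1 − exp(−3h)) + f(1 − exp(−3mh)) = 0.31 for h, the hazard of those who stay. The observed HR is h(test)/h(control).

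| Terminated, test v control | m = 1 | m = 1.5 | m = 2 | m = 3 |
|---|---|---|---|---|
| 10% v 10% | 1.00 | 1.00 | 1.00 | 1.00 |
| 10% v 5% | 1.00 | 0.98 | 0.96 | 0.93 |
| 15% v 5% | 1.00 | 0.96 | 0.92 | 0.87 |

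With z = ln(HR) × √events/2, the two-sided rejection rate is Φ(−1.96 − z) + 1 − Φ(1.96 − z). For 15% v 5% it is 5.0%, 5.6%, 6.8% and 10.2% across the four columns. If the larger share left from control instead, the bias would run the other way.

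**The case against.** The strongest reply is that section 2.3.4 states no rule to stop collecting outcomes. Items a and b are worded around treatment, and so is inability to take the medicine. The sections that govern follow-up all point to continued observation. That is fair: the text is ambiguous and does not instruct sites to censor. But 2.3.4 speaks of participation, trial termination and withdrawal, and never says that follow-up continues, so the conflict stands.

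Four stronger readings are tempting, and the document does not support them.

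- *DFS is informatively censored.* No section gives a censoring rule for terminated cases. Bias needs both unequal exit and different prognosis, and neither is documented in a double-blind trial with a matched placebo.
- *The intention-to-treat analysis is lost.* Section 2.10.1 aims at all randomised participants with the smallest elimination. It makes absence of major violations a condition of the compliance scheme set only, and it does not link case termination to removal from the full analysis set. Detailed exclusion grounds may sit in documents not shown. What remains is that the sentence, read literally, eliminates everyone.
- *Inability to take the medicine counts as an end of observation.* Item e defines the endpoint in its parenthesis as recurrence or metastasis, and the inability is a separate alternative in the same item.
- *Allergy cases are imputed as DFS failures.* The remark on ineffective treatment is tied to no outcome. Table 1 has a category of that name for the TCM Symptom Scale, which may be where it belongs.

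It can also be said that the 5% annual loss already covers such exits. In part it may. But 5% a year amounts to 1 − 0.95^0.25 = 1.3% over the 3-month treatment phase, so a larger early exit would exceed it.

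**Conclusion.** The point holds as a conflict over who stays under observation for the primary endpoint, and on that confidence is high. Its effect on the result is a risk whose size the document does not fix. Under balanced exit, power falls below the planned 80% once more than about 5% of each arm is terminated early without follow-up, given the section 2.9 event rates and the full 5% annual loss on top. The bias figures rest on assumed exit shares and assumed hazards in leavers. The 15% v 5% row is the unfavourable end, with every leaver at raised risk, and should not be read as a forecast. The conflict should be corrected before it affects data collection, because follow-up that was never collected cannot be restored in the analysis.

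**What to change.** 1. Leave the clinical reasons for stopping treatment as they are, and reconcile section 2.3.4 with 2.7.1 and 2.7.3. State that severe adverse events, allergic discontinuation, plan violation and inability to take the medicine end study medication only. State that recurrence, metastasis and death are still collected at the planned visits and calls to study end, unless the patient withdraws consent to follow-up.
2. Rewrite the full-analysis-set sentence in section 2.10.1 so that DFS is analysed in all randomised participants, in the arm to which they were randomised.
3. State in section 2.3.4 that the remark on ineffective treatment does not apply to DFS, and name the outcome to which it does apply.

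The cost is protocol wording and a note to the sites. The visits in Table 2 and the telephone contact in section 2.7.3 are already planned.
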